### Assessment of safety

Adverse events (AEs) will be obtained by researchers by inquiring of the participants at each treatment or follow-up visit or by voluntarily reporting by the participants. Information of AEs will be appropriately documented throughout the trial. Acupuncture-related AEs include intolerable needling pain, bleeding after needle withdrawal, hematoma, and local infection. AEs related to COH include pain, organ injury, colporrhagia, and infection caused by egg retrieval, ovarian hyperstimulation syndrome, thrombosis, and allergic reaction.

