## Methods

### Study design

This will be an exploratory multicenter randomized controlled trial comparing acupuncture with nontreatment. A total of 140 women with POR will be recruited from the following 9 hospitals in China: Shanxi Provincial Hospital of Chinese Medicine, Shandong University Reproductive Hospital, Sun Yat-sen Memorial Hospital of the Sun Yat-sen University, Lanzhou University First Hospital, People’s Hospital of Henan Province, Huazhong University of Science and Technology Reproductive Medicine Center of Tongji Medical College, Shanghai Shuguang Hospital, Nanjing General Hospital of Nanjing Military Command, and Luoyang Women and Children Health Care Center. This protocol is in accordance with the principles of the Declaration of Helsinki. It was approved by the ethics committee of each participating hospital. Written informed consent will be obtained from patients prior to enrolment.

Eligible patients will be randomly assigned to receive acupuncture or nontreatment for 12 weeks, which will be followed by an IVF cycle. Outcomes will be assessed at baseline, after acupuncture or nontreatment intervention, and after the IVF cycle. The flowchart and study design schedule are presented in Fig. 1 and Table 1, respectively. This protocol has been registered at Acupuncture-Moxibustion Clinical Trial Registry (AMCTR-IPR-18000198).

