### Interventions

#### Acupuncture protocol

Patients in the acupuncture group will receive a 12-week acupuncture treatment regimen before COH. Acupuncture will be performed by registered acupuncturists with over 2 years of experience. Hwato brand disposable acupuncture needles (size 0.25 × 25 mm, size 0.25 × 40 mm, and size 0.30 × 75 mm) and SDZ-III electroacupuncture apparatuses (Suzhou Medical Appliance Factory, Suzhou, China) will be used.

The acupuncture protocol designed for this trial is based on our clinical practice for improving ovarian function for women with DOR [14]. It consists of two groups of acupoints: Group 1 (in supine position): GV20 (Baihui), GV24 (Shenting), GB13 (Benshen), CV12 (Zhongwan), ST25 (Tianshu), CV4 (Guanyuan), KI12 (Dahe), EX-CA1 (Zigong), SP6 (Sanyinjiao), KI3 (Taixi), LR3 (Taichong); and group 2 (in prone position): BL23 (Shenshu) and BL33 (Zhongliao). These two groups of acupoints will be used alternatively with group 1 as the initial treatment. All acupoints will be located according to the World Health Organization Standardized Acupuncture Points Location [19]. A needle depth of 10 to 20 mm will be applied for GV20, GV24, and GB13 with transverse insertion and for LR3 with oblique insertion to the direction of KI1 (Yongquan). BL33 will be needled with an oblique downward trajectory of approximately 60 to 70 mm into the third posterior sacral foramina. The remaining acupoints will be perpendicularly needled for approximately 30 to 40 mm. After insertion, small, equal manipulations of lifting, thrusting, or twirling will be performed on all needles (for GV20, GV24 and GB13, twirling only) to reach deqi, a composite of sensations (including soreness, numbness, distention, and heaviness) recognized as an essential component in achieving the acupuncture effect. In acupuncture with acupoints of group 2, paired electrodes from the electroacupuncture apparatus will be attached transversely to the needle handles at bilateral BL23 and BL33 with a dilatational wave and a current intensity that patients can tolerate (preferably with the skin around the acupoints shivering mildly without pain). Each acupuncture session will last for 20 min. Participants will receive 3 sessions of acupuncture per week (ideally every other day) for 12 consecutive weeks for a total of 36 sessions.

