#### Nontreatment control

Participants in the control group will receive nontreatment for 12 weeks before COH.

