#### COH regimen

Participant will start COH with a GnRH antagonist protocol on day 2 or 3 of the menstrual cycle after acupuncture or nontreatment period. GnRH antagonists are commonly used to prevent the premature LH surge that often occurs in poor responders [20, 21]. This induces pituitary suppression within a few hours without a flare-up effect, and the suppression is released immediately after their discontinuation [22]. Compared with GnRH agonist, GnRH antagonist protocol shows a shorter treatment time, a lower dosage of Gn, and a similar clinical pregnancy rate [5]. In this trial, individualized GnRH antagonist protocol will be administered by physicians of reproductive medicine in each center. Given that participants may become suitable for COH before they complete the 12-week acupuncture or nontreatment, an early termination of acupuncture or nontreatment aiming to seize the opportunity to initiate a COH cycle will be allowed on the condition that they complete at least the 4-week acupuncture treatment (12 sessions of acupuncture) or nontreatment period.

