### Data management and quality control

A pretrial training will be done for all participating staff on the trial protocol, acupuncture manipulation, usage of the central randomization, and data management systems, etc. Double data entry will be applied in this trial to ensure the accuracy of data entry. A three-level quality control system (including self-inspection of each center, monitoring by project management group, and auditing by a third party) will be applied to ensure the implementation, recording, and reporting of clinical trials conform to the trial protocol, standard operation specifications, and relevant laws and regulations. Self-inspection will be done at least once every month by the quality controller of each center. On-site or remote monitoring will be done for all centers once every 3 months by the monitors appointed by the principle investigator. The auditing will be done by Clinical Evaluation Center of the China Academy of Chinese Medical Sciences at the beginning, middle, and end of the trial. An ethics committee will review conduct especially on safety, rights, and well-being of the participants at the middle and the end of the trial. Regular reminders via WeChat will be used to improve participant compliance. For patients who discontinue or deviate from the protocol, causes and relevant outcome data will be recorded in a case report form as much as possible.

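### Active adverse-event enquiry is tied to acupuncture sessions that controls do not have, so any between-arm comparison of non-needling events before COH is open to ascertainment bias

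*Protocol article*

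**What the plan says.** Under Assessment of safety, the protocol article obtains AEs "by inquiring of the participants at each treatment or follow-up visit", or from women who report them unprompted. The Acupuncture protocol section sets "3 sessions of acupuncture per week (ideally every other day) for 12 consecutive weeks for a total of 36 sessions". The COH regimen section lets women move to COH early, provided that they "complete at least the 4-week acupuncture treatment (12 sessions of acupuncture) or nontreatment period". For the other arm, the Nontreatment control section says only: "Participants in the control group will receive nontreatment for 12 weeks before COH".

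The Study design section states: "Outcomes will be assessed at baseline, after acupuncture or nontreatment intervention, and after the IVF cycle". Table 1 agrees and marks AEs at W0, W12 and W14.

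The AEs that the article names fall into two classes. The first is needling events: "Acupuncture-related AEs include intolerable needling pain, bleeding after needle withdrawal, hematoma, and local infection". The second is events of egg retrieval and ovarian stimulation. The Abstract says that the safety of acupuncture will be assessed. The Statistical analysis section names no test for AEs. It gives one general rule for categorical variables, a chi-square or Fisher exact test between groups, and makes no exception for AEs.

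**The concern.** The rule makes the number of times a woman is asked about AEs depend on her arm. A mild, short-lived event in the 12 weeks before COH is asked about within days if she is on acupuncture. If she is a control, it reaches the record only if she reports it unprompted or still recalls it at W12.

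For events that can occur in either arm, the control arm supplies the background rate against which acupuncture is judged. If that rate is under-recorded, acupuncture can look less safe than it is. Later analysis cannot recover events that nobody asked about, so this is a matter of data collection and not a detail that an analysis plan could settle afterwards.

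**Working it through.** **1. The article's session count.** Sessions = sessions per week × weeks. Full course: 3 × 12 = 36, which reproduces the stated total. Shortest permitted course: 3 × 4 = 12, which reproduces the stated minimum.

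**2. Scheduled active enquiries by arm.** Inputs are the enquiry rule (Assessment of safety), the session counts from step 1, the absence of treatment visits on control (Nontreatment control) and the AE row of Table 1.

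| Period | Acupuncture | Control |
|---|---|---|
| After W0 and before the W12 assessment | 12 to 36 | 0 shown |
| Including the W12 assessment (+1 in each arm) | 13 to 37 | 1 |

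The control zero is read from Table 1 and from the lack of any described interim visit. The article does not state it outright.

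**3. Which AEs are exposed.**
- Needling events arise in one arm only, so there is no between-arm contrast to distort.
- COH events arise after the intervention period, on the same schedule in both arms.
- What remains is any other AE before COH.
- The primary outcome, the oocyte count, does not come from AE enquiry.

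**4. Illustration of size (all inputs assumed).** With the same true risk in both arms, apparent risk ratio = capture on acupuncture ÷ capture on control.

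- Assumed 90% capture at sessions and 30% to 60% by recall: 0.90/0.60 = 1.5, and 0.90/0.30 = 3.0.
- Assumed full capture on acupuncture and 75%, 50% or 25% on control: 1.33, 2.0 and 4.0.

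For the second set, the chance of a spurious p < 0.05 against acupuncture with n = 70 per arm (no dropout) is approximately

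Φ{ [ (p₁ − p₂) − 1.96·√(2p̄(1 − p̄)/n) ] / √( [p₁(1 − p₁) + p₂(1 − p₂)]/n ) }.

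Worked case, p₁ = 0.20 and p₂ = 0.20 × 0.50 = 0.10, so p̄ = 0.15: the two standard errors are 0.0604 and 0.0598, and (0.10 − 1.96 × 0.0604)/0.0598 ≈ −0.31, so Φ ≈ 0.38.

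| True risk, both arms | Control capture 75% | 50% | 25% |
|---|---|---|---|
| 10% | 7.5% | 20% | 45% |
| 20% | 12% | 38% | 77% |
| 30% | 17% | 57% | 93.5% |

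With equal capture the figure is the nominal 2.5% in that direction, and there is no bias.

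**The case against.** Much of the opposing case is sound.

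- **No interim control contact is an inference.** Table 1 is condensed. It does not show the 36 sessions either, and the AE mark sits under a column headed Intervention. The enquiry rule also covers follow-up visits, and the full protocol may schedule some for controls. This stands, and it is why the point says that none is shown. It does not restore balance, because extra control visits would have to match a thrice-weekly schedule to do so.
- **Controls are not unobserved.** Voluntary reporting is open to both arms, and the W12 enquiry can pick up earlier events by recall. This stands.
- **No AE-specific comparison is planned.** AEs are not among the listed primary or secondary outcomes, and the general categorical rule does not mention them. This stands, so the point applies to any comparison that is made.
- **The named AEs are mostly outside the problem.** This stands for the reasons in step 3.
- **The likely direction is cautious**, overstating harm on acupuncture. This is fair, but a stated aim is to assess the safety of acupuncture, and error in either direction weakens that.

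A reader might infer that the safety comparison is already biased, at 36 enquiries against none. The documents do not support this. Thirty-six is the full-course maximum, the W12 enquiry is common to both arms, and no capture rate is given from which a bias could be shown. Nor can the risk ratio of 1.5 to 3.0 be read as an estimate, since it is only a ratio of two assumed capture rates.

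**Conclusion.** The point holds in a limited form. As written, the enquiry rule gives unequal active ascertainment before COH: up to 36 session enquiries on acupuncture (at least 12 with early COH), against none shown for controls until W12. A between-arm comparison of non-needling AEs in that period is open to bias, most likely against acupuncture.

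The size cannot be computed from the documents. The apparent risk ratios of 1.33 to 4.0 show only what unequal capture could do under the stated assumptions. The conclusion rests on two things: that no regular control contact exists beyond what the article shows, and that non-needling AEs will be compared between arms. If either fails, the concern shrinks or disappears. It does not reach the primary outcome.

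**What to change.** In Assessment of safety and Statistical analysis, state before analysis that:

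1. the record of each AE shows which enquiry, or unprompted report, captured it;
2. any between-arm AE comparison uses only the enquiries common to both arms (W0, W12 and W14), with the same question put in the same way;
3. AEs noted at acupuncture sessions, including needling events, are reported descriptively for that arm.

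The cost is slightly more data recording and fewer mild events in the between-arm comparison. Some imbalance may remain, because women asked at every session may recall more at W12.

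Matching interim AE contacts in both arms may be added where feasible. The existing messages are a possible route ("Regular reminders via WeChat will be used to improve participant compliance"), but the article does not give their frequency or say whether controls receive them. The trial is already recruiting at nine hospitals, so a new questionnaire would probably need an amendment and would make AE collection differ between earlier and later participants. Steps 1 to 3 do not depend on it.

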### Data management and quality control

A pretrial training will be done for all participating staff on the trial protocol, acupuncture manipulation, usage of the central randomization, and data management systems, etc. Double data entry will be applied in this trial to ensure the accuracy of data entry. A three-level quality control system (including self-inspection of each center, monitoring by project management group, and auditing by a third party) will be applied to ensure the implementation, recording, and reporting of clinical trials conform to the trial protocol, standard operation specifications, and relevant laws and regulations. Self-inspection will be done at least once every month by the quality controller of each center. On-site or remote monitoring will be done for all centers once every 3 months by the monitors appointed by the principle investigator. The auditing will be done by Clinical Evaluation Center of the China Academy of Chinese Medical Sciences at the beginning, middle, and end of the trial. An ethics committee will review conduct especially on safety, rights, and well-being of the participants at the middle and the end of the trial. Regular reminders via WeChat will be used to improve participant compliance. For patients who discontinue or deviate from the protocol, causes and relevant outcome data will be recorded in a case report form as much as possible.

### Statistical methods

#### Sample size calculation

There are no available clinical studies on the effect of acupuncture for POR. Based on results of a TEAS study on POR [18], we assumed the mean (SD) number of retrieved oocytes would be 4.88 (1.84) in the acupuncture group and 3.95 (1.66) in the control group. A sample size of 57 participants per group would be needed to provide 80% power and a two-sided significance level of 5%. Allowing for a 20% dropout rate, 140 participants will be recruited with 70 participants per group.

#### Statistical analysis

Statistical analysis will be performed by a statistician blinded to group assignments using SAS version 9.4 (SAS Institute Inc). All analyses will be based on the intention-to-treat principle. Missing data will be imputed using the multiple imputation method. Continuous data will be presented as the mean and standard deviation, or the median and interquartile range; categorical data will be presented as the number and percentage. Comparisons between groups will be analyzed using an independent *t*-test or Wilcoxon rank-sum test for continuous variables, and a chi-square test or Fisher exact test for categorical variables. All statistical tests will be two-sided, and *p* < 0.05 will be considered statistically significant.

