### Randomization and masking

Block randomization stratified by center will be applied in this trial. Eligible participants will be randomly assigned to acupuncture or nontreatment groups in a 1:1 ratio. The scheme of randomization including any planned restriction (e.g., blocking) will be designed and archived by a statistician who will not be involved in the statistical work of this trial. The allocation sequence will be computer-generated. If a participant is eligible for the trial, the appointed researcher (acupuncturist or reproductive physician) in each center will apply for the random number and group assignment via a telephone- and internet-based central randomization system of the Clinical Evaluation Center of the China Academy of Chinese Medical Sciences. A strict view permission will be set for the central randomization system, which allows no one except the top system administrator to view its randomization scheme. In this study, outcome assessors and data analysts will be blinded to group allocation.

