### Outcome measures

The primary outcome is the number of retrieved oocytes. The secondary outcomes include the assessment of ovarian reserve (AFC and serum levels of AMH, FSH, LH, and E2), other IVF outcomes (fertilization rate, cleavage rate, available embryo rate, and high-quality embryo rate), and the score of the self-rating anxiety scale (SAS). Ovarian reserve will be assessed at baseline and after acupuncture or nontreatment period. AFC (via transvaginal ultrasound) and serum levels of FSH, LH, and E2 are required to be measured on days 2 to 5 of the menstrual cycle. AMH can be measured on any day of the menstrual cycle. SAS is a self-rating scale for measuring the presence and severity of anxiety [23]. A validated Chinese version of SAS will be used [24]. It consists of 20 items rated on a 4-point Likert scale. When using the scale, participants will be asked to rate each item from 1 to 4 points according to how it applies to them within the past week. The standard score is the sum of the integer part of 1.25 times the raw score (the sum of the 20 items ranging from 20 to 80). The presence of anxiety symptoms is defined as an SAS standard score of greater than 50. A higher score indicates a more serious case of anxiety. SAS will be assessed at baseline and after acupuncture or nontreatment period.

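### Randomisation is stratified by centre, but the primary comparison is an unadjusted t-test or Wilcoxon test that ignores centre and baseline AFC and AMH

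*Protocol article*

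**What the plan says.** Four parts of the protocol article bear on this.

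- **Design.** Study design: "A total of 140 women with POR will be recruited from the following 9 hospitals in China". Randomization and masking: "Block randomization stratified by center will be applied in this trial", with women "randomly assigned to acupuncture or nontreatment groups in a 1:1 ratio".
- **Outcome and baseline data.** Outcome measures: "The primary outcome is the number of retrieved oocytes". The same section states "Ovarian reserve will be assessed at baseline and after acupuncture or nontreatment period", and Table 1 schedules AFC and AMH at week 0.
- **Analysis.** Statistical analysis assigns every continuous variable, and so the primary outcome, to an independent t-test or "Wilcoxon rank-sum test for continuous variables, and a chi-square test or Fisher exact test for categorical variables". It adds intention-to-treat and multiple imputation for missing data. It mentions no centre term, stratified test, covariate or model.
- **Sample size.** Sample size calculation assumes means (SDs) of "4.88 (1.84) in the acupuncture group and 3.95 (1.66) in the control group" and arrives at 57 per group for 80% power at two-sided 5%, which is also an unadjusted two-sample calculation.

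**The concern.** Blocking within centre keeps the arms nearly balanced in every hospital, so differences between hospitals largely cancel out of the arm difference. A plain t-test or rank-sum test does not know this and still counts between-centre variation as noise. The analysis therefore does not match the design. If centres differ, the reported standard error is larger than the true one, the p-value is too large on average, and the interval is too wide.

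Baseline AFC and AMH raise a separate question of efficiency. They are the trial's own measures of ovarian reserve, and the Background ties low reserve to poor response to stimulation. They are collected before treatment, yet the primary comparison makes no use of them. At stake is the precision of the primary estimate, in a trial with little power to spare.

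**Working it through.** **Inputs from the documents.** Difference 4.88 − 3.95 = 0.93 oocytes; SDs 1.84 and 1.66; 57 per group; nine centres; 1:1 allocation in blocks within centre.

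**Inputs assumed.** The documents give neither the share of variance between centres (ICC) nor the share explained by baseline AFC and AMH (R²), so both are shown as ranges. Block size is not stated either; the simulations use 4.

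**1. The plan's own figure.** Pooled SD = √[(1.84² + 1.66²)/2] = 1.752. The normal approximation gives 56 per group. The exact t-test solution is 56.7, so 57, with power 80.2%. The stated 57 reproduces.

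**2. Size of the unadjusted test when centre is ignored.** With exact balance within centres, the true variance of the difference is (1 − ICC) times what the t-test assumes. True size = 2Φ(−1.96/√(1 − ICC)).

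- ICC 0: 5.0%.
- ICC 0.05: 1.96/√0.95 = 2.011, so 4.4%.
- ICC 0.15: 1.96/√0.85 = 2.126, so 3.4%.

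**3. Simulation check.** 114 women in nine near-equal centres, permuted blocks of 4, normal outcomes; 5,000 null and 2,500 alternative replicates per setting. With no baseline covariate effect:

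| ICC (assumed) | Size: t-test / with centre | Half-width: t-test / with centre | Width ratio | Power: t-test / with centre |
|---|---|---|---|---|
| 0 | 4.6% / 4.5% | 0.648 / 0.650 | 1.00 | 79.8% / 80.0% |
| 0.05 | 4.4% / 4.7% | 0.647 / 0.634 | 1.02 | 80.0% / 80.6% |
| 0.10 | 4.5% / 5.3% | 0.645 / 0.617 | 1.05 | 81.4% / 83.2% |
| 0.20 | 3.3% / 5.1% | 0.642 / 0.583 | 1.10 | 82.4% / 87.4% |

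The Monte Carlo standard error is about 0.3 points for size (√(0.05 × 0.95/5000)) and 0.8 points for power (√(0.8 × 0.2/2500)). The effect at ICC 0.05 is therefore close to noise, while at 0.20 it is clear. The simulated size at a given ICC can lie a little above the formula, because incomplete blocks leave some imbalance within centres.

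**4. Precision from centre and baseline together.** Let R² be the share of variance that they jointly explain. Residual SD = 1.752 × √(1 − R²); half-width = 1.96 × residual SD × √(2/57); power = Φ(0.93/SE − 1.96).

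| R² (assumed) | Residual SD | 95% CI half-width (oocytes) | Power at 57 per group |
|---|---|---|---|
| 0 | 1.752 | 0.64 | 81% |
| 0.10 | 1.662 | 0.61 | 85% |
| 0.20 | 1.567 | 0.58 | 89% |
| 0.30 | 1.466 | 0.54 | 92% |

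The 81% in the first row is the normal approximation to the 80.2% in step 1.

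**5. Cost of adjusting for nothing.** At ICC 0 and R² 0, the simulated half-width is 0.648 unadjusted and 0.653 with centre and one covariate. Arm, nine centre terms and two covariates use 12 parameters, leaving 114 − 12 = 102 residual degrees of freedom.

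**Limit of the check.** The simulated model has one generic normal covariate, complete data and model-based standard errors. It shows direction and rough size, not the exact performance of the model proposed below.

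**The case against.** The best defence is that nothing planned is lost. The sample size rests on raw SDs and an unadjusted comparison, and that comparison delivers the planned 80%. Any error is conservative. The trial calls itself exploratory, the section is a short summary in a journal article, and covariate models are often left to an analysis plan. Most of this stands and limits the weight of the point. It does not remove it: the article itself names the tests, they do not reflect the stratification it describes, and it sizes the trial for 80% power and tests at 5%.

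Four stronger readings are tempting, and the documents do not support them.

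- **That a centre effect is certain because each centre has its own stimulation regimen.** The COH regimen section says "individualized GnRH antagonist protocol will be administered by physicians of reproductive medicine in each center". All centres use the antagonist protocol, and the Background describes individualising by ovarian reserve, which is by patient. A centre effect is plausible but not documented.
- **That omitting AFC and AMH makes the test wrong.** It does not. Chance imbalance in ovarian reserve is random error that the unadjusted standard error already covers. Only precision is forgone.
- **That a Wilcoxon test cannot be combined with multiple imputation.** It can: the Mann–Whitney probability, the Hodges–Lehmann shift or the standardised statistic can be pooled.
- **That adjustment would bring power to about 90%.** That needs an R² of about 0.20 or more. Eligibility requires at most three oocytes in a previous cycle, plus low AFC or AMH or two poor-response episodes. This narrows the covariate range and may keep R² low.

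**Conclusion.** The point holds as a mismatch between design and analysis with modest consequences. Omitting centre makes the primary test mildly conservative only if centres differ: true size is about 4.4% at an assumed ICC of 0.05 and 3.4% at 0.15, with no material effect at 0. In simulation, intervals are about 2%, 5% and 10% wider than with centre in the model at ICCs of 0.05, 0.10 and 0.20. Omitting baseline AFC and AMH leaves a valid test. Across an assumed joint R² of 0 to 0.30, adjusting for centre and baseline would shorten the half-width from about 0.64 to 0.54 oocytes and raise power from about 81% to 92%.

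A reader might infer that the trial is underpowered or at risk of a false positive. Neither follows: 57 per group reproduces, and the error runs in the conservative direction. The textual mismatch is certain. The size of the gain is not, because it rests wholly on an ICC and an R² that the documents do not give. The change is still worth making, since it costs almost nothing even if both are zero.

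**What to change.** Before unblinding, replace the open choice of tests for the primary outcome with one pre-specified linear model: number of retrieved oocytes on arm, centre, baseline AFC and log baseline AMH. State a rule for pooling very small centres; 140 women in nine hospitals average about 15.6 each, and recruitment may be uneven. Report the adjusted mean difference with its 95% CI, pooled across imputations by Rubin's rules. Keep a centre-stratified (van Elteren) rank test or a robust count model as sensitivity analysis.

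If a separate analysis plan already specifies such a model, bring the two documents into line. The cost is analysis wording only: no new data, visits or participants, and no change to the sample size.
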